## Background

Drug-related problems (DRP) are a major concern in terms of public health because they have a serious clinical and economic impact on healthcare systems. A French multicentric study [1] reported that adverse drug events (ADE) were the second most common complication during hospitalization and were responsible for around 130,000 hospitalizations and 10,000 deaths a year in France. Apretna et al. estimated that each ADE cost > €5000 on average [2], yet around half of the severe ADEs are considered to be preventable [1]. Medication errors that can lead to ADE mainly occur at transition points in the patient’s healthcare pathway, mostly due to defects in the transmission of information at the prescription and the administration steps [3]. Also, 47–67% of patients have at least one error or discrepancy between the medications prescribed in the community and in the hospital. These errors are responsible for severe ADEs in 18–59% of cases [3–6]. Elderly patients are frequently frail and are at particularly high risk of DRPs. Indeed, 32–46% of hospitalized elderly patients experience at least one ADE [7, 8], of which 28% were deemed to be preventable [9].

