### Outcomes

The primary outcome will assess the rate of patients having at least one preventable medication error (e.g. omission, wrong dose, wrong route of administration, etc.) on admission medication order (AMO). The primary outcome will be evaluated by clinical pharmacists retrospectively in the control period and prospectively in the interventional period.

Among the secondary outcomes, the potential clinical impact of each error detected will be assessed by a hospital physician and two clinical pharmacists (different from the investigators) by using a decision algorithm [30] adapted from the NCC MERP’s Index [31] and employing the high alert risk medication list of the Institute of Safe Medication Practices [32] and the North Carolina Narrow Therapeutic Index [33]. All of the experts, who are seniors specialized in geriatrics, will blindly perform the analysis, i.e. without knowing the hospital center concerned, after completion of patient recruitment for all the centers. The potential clinical impact will also be evaluated by the rate of patients at high risk of ADEs according to Trivalle’s score [9, 34].

Other secondary outcomes will be: (1) the acceptance rate of pharmaceutical interventions during the interventional period; (2) the readmission and mortality rates 30 and 90 days after discharge; (3) the length of hospital stays; (4) the satisfaction of care providers involved in the collaborative pharmaceutical care (assessed by postal or electronic mail after the end of the 90-day follow-up); and (5) the induced and avoided costs of the strategy. For this last outcome, we will estimate the induced costs by measuring the time spent performing the collaborative pharmaceutical care. We will also assess the avoided costs by estimating the healthcare consumptions dues to medication errors by using the results of a French national study concerning ADE occurrence and cost [1] and/or by using an expert concertation via a DELPHI method.

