The economic study proposed is in the form of a cost-consequence one, using the decision tree methodology. The decision tree is a decision support tool that uses a tree-like graph or model of decisions and their possible consequences, including chance event outcomes and/or resource costs. Each node of the tree is associated to a probability and each trajectory is associated to a leaf and a cost. A stochastic analysis will be performed. All probabilities will be associated to a beta distribution and 10,000 Monte Carlo simulations will estimate the mean cost and the associated confidence interval of each group (without vs with pharmacist). The robustness of the results will be checked with the sensitivity analysis. This will be done by performing a second estimation including a new set of parameters in the decision tree, in order to consider the uncertainty due to the sample, specifically on event probabilities and individual costs induced. If the results of global cost are unchanged, then the robustness could be deduced. The Tornado diagram will be used to evaluate and sort the most sensitive parameter.

The Department of Biostatistics, Epidemiology, Public Health, and Health Economics of Nîmes Hospital Center will perform the statistical analysis using R.4.0. (R Development Core Team [2017], R Foundation for Statistical Computing, Vienna, Austria; https://www.r-project.org) and TreeAge Pro 2017 (TreeAge Software, Williamstown, MA, USA; https://www.treeage.com).

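### The economic simulation assigns distributions to probabilities only and reports cost intervals per group; cost uncertainty sits in a separate check with no usable criterion

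*Protocol article*

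**What the plan says.** The economic part of the Statistical analysis section describes a decision tree in which "Each node of the tree is associated to a probability and each trajectory is associated to a leaf and a cost". A stochastic analysis follows: "All probabilities will be associated to a beta distribution and 10,000 Monte Carlo simulations will estimate the mean cost and the associated confidence interval". The target of that interval is "the mean cost and the associated confidence interval of each group (without vs with pharmacist". No interval for the difference between the groups is named.

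Costs come back in the sensitivity analysis: "This will be done by performing a second estimation including a new set of parameters in the decision tree". The stated purpose of that second run is to cover sampling uncertainty, both in the event probabilities and in the individual costs. The rule for judging it is: "If the results of global cost are unchanged, then the robustness could be deduced". A Tornado diagram then ranks the parameters by influence.

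The Outcomes section shows where the costs come from. Induced cost rests on measured time spent on the pharmaceutical care. Avoided cost rests on a French national study "and/or by using an expert concertation via a DELPHI method".

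**The concern.** Each path through the tree ends in a cost, and those costs are estimates: one from timed work, the other from an outside study or expert elicitation. The only distributions named for the 10,000 draws are those on probabilities. If the simulation is run that way, the interval for mean cost treats the cost inputs as known. The article itself lists individual costs as a source of sampling uncertainty, but places that uncertainty in a second run that does not feed the interval.

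Two further features weaken the result. The economic question is whether avoided costs exceed induced costs, yet the stated intervals belong to each group separately. And a new parameter set will practically always move the mean cost, so a rule that asks for an unchanged result, with no tolerance or decision criterion, cannot be applied as worded.

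At stake is the precision claimed for the economic result. The Discussion expects a professional society to write recommendations and promote implementation of this care nationally.

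**Working it through.** The article states no cost interval, so there is no figure of the plan to reproduce. The check below only illustrates direction and possible size.

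**Inputs from the article**
- Control error rate 0.46; with the assumed difference of 0.30, the intervention rate is 0.46 − 0.30 = 0.16 (Sample size calculation).
- Patients per condition: the switch periods in Table 1 give 1+2+3+4+5+6 = 21 control cells out of 42, so 21 × 15 = 315 control and 315 intervention patients.
- Probability q of a severe adverse drug event given an error: 0.18 or 0.59, the ends of the range in Background.
- Unit cost €5000, from Background: "each ADE cost > €5000 on average".

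**Assumptions, not in the article**
- Relative standard error r of the unit cost: 10%, 20% or 30%, gamma distributed.
- q estimated from 195 patients with an error (0.46 × 315 + 0.16 × 315 ≈ 195).
- q and the unit cost are shared by both groups. Pharmacist time and clustering are left out.

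**Formula.** Avoided cost per patient is (p0 − p1) × q × C, and control cost is p0 × q × C. For a product of independent factors, relative variances add approximately. If V is the relative variance from the probabilities alone, letting C vary multiplies the interval width by about √(1 + r²/V).

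**Relative variances**
- p0: 0.54/(0.46 × 315) = 0.00373
- p0 − p1: (0.46 × 0.54 + 0.16 × 0.84)/(315 × 0.30²) = 0.3828/28.35 = 0.01350
- q = 0.18: 0.82/(0.18 × 195) = 0.02336
- q = 0.59: 0.41/(0.59 × 195) = 0.00356

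**Difference**
- q = 0.18: V = 0.01350 + 0.02336 = 0.03686. At r = 0.10, √(1 + 0.01/0.03686) = 1.13; at r = 0.20, √(1 + 0.04/0.03686) = 1.44.
- q = 0.59: V = 0.01350 + 0.00356 = 0.01706. At r = 0.10, 1.26; at r = 0.20, 1.83.

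A simulation of 400,000 draws, with beta distributions on the probabilities and a gamma on the cost, gives these width ratios (the ranges span q = 0.18 to 0.59):

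| r | Control group | Difference |
|---|---|---|
| 10% | 1.2–1.5 | 1.1–1.3 |
| 20% | 1.6–2.6 | 1.5–1.8 |
| 30% | 2.1–3.7 | 1.9–2.5 |

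Example at q = 0.18 and r = 20%: control cost goes from €291–557 to €236–656, and the difference from €178–380 to €147–441.

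**Per-group intervals.** Under the sharing assumption, the two groups' draws correlate at about 0.3 to 0.9. Combining the two group intervals as if independent would give a difference interval 1.16 to 1.57 times too wide. The difference has to be taken within each draw.

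**With pharmacist cost.** A second run of 10,000 draws used q = 0.18 with effective sample size 300, an assumed €60 pharmacist cost per patient, and the same r on both costs. The net cost (with minus without pharmacist) goes from −€307 to −€126 out to −€326 to −€116 at r = 10% (ratio 1.16), and from −€305 to −€127 out to −€369 to −€88 at r = 20% (ratio 1.58). The interval reaches zero only at r = 50% (−€561 to €1).

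**The case against.** The strongest reply is that this is a condensed article and the table of input distributions may sit in a fuller document. The text says that all probabilities get a beta distribution; it does not say that nothing else varies. A reader might infer that the plan fixes costs as constants or ignores their uncertainty. The documents do not support that: the same paragraph sends cost uncertainty to a second estimation and a Tornado diagram. A second tempting inference is that no valid interval for the difference could be had. That fails too, because the same 10,000 draws would yield it directly, and nobody proposes to combine the two group intervals. Leaving the avoided-cost source as one or both of two options is missing detail, not an error. *Unchanged* may also have been meant as no material change.

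The illustration has limits as well. The relative standard error of the cost is assumed. The €5000 is a lower bound, from a different cited study than the one named for avoided costs. The direction of the result survives in most scenarios.

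What stands against this reply is the method as stated. Distributions are named for probabilities, the interval comes from those draws, and costs are handled in a separate run. Neither that run nor a ranking of parameters enters the reported interval. The robustness rule is stated text, and even on a charitable reading it has no threshold.

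**Conclusion.** The point holds in a limited form. Followed as written, the per-group intervals omit uncertainty in unit cost and pharmacist time and are too narrow. The direction is secure provided cost uncertainty is independent of the probabilities. The size cannot be derived from the documents: it could be small, about 10% to 30% for the difference at an assumed 10% relative standard error, or substantial, about 50% to 80% at 20%. The stated intervals do not target the contrast that the economic question asks about, and the robustness rule cannot be applied as worded. The documents do not show that the economic conclusion would change; in the illustration with pharmacist cost, the net saving excluded zero at relative standard errors up to 30%. Only a secondary outcome is affected.

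**What to change.** In the economic paragraph of Statistical analysis:

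1. Give unit costs and measured pharmacist time distributions in the same 10,000 draws, for example gamma for unit costs and gamma or bootstrap for time.
2. Compute net cost, with minus without pharmacist, within each draw, drawing any shared parameter once. Report it with its 95% interval beside the group means.
3. Replace the unchanged rule with a usable criterion, such as the same sign of the net cost and the same conclusion under the alternative parameter set.

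No new data are needed. The cost is some rewording, a few more distributions in a simulation already planned, and wider reported intervals.

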### Design

A multicentric stepped wedge cluster randomized trial is proposed because randomization of patients was not possible in this study due to the high risk of contamination bias. Indeed, once the clinical pharmacist arrives in the care unit, the collaborative pharmaceutical care will lead to change in medical practices for all the patients, including the control group. Stepped wedge randomized trial designs involve sequential roll-out of an intervention to participants over a number of time periods. By the end of the study, all participants will have received the intervention, although the order in which participants receive the intervention is determined at random. The clusters will be hospital units. Each hospital unit will start with a control period and switch to an interventional period. The study design will be composed of seven consecutive 14-day periods (Fig. 1). Every 14-day period, one further hospital unit will switch to the interventional period until all the units are in the interventional period in the final 14-day period. The randomization by the project methodologist will define the point that each hospital unit will switch from the control to the interventional periods (Table 1).

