### Sample size calculation

A stepped wedge trial was designed according to a validated methodology [39]. A previous study showed that the rate of patients with at least one medication error in the AMO was 46% and 2% for the control and experimental strategies, respectively [11]. In order to make more conservative assumptions, we decreased the expected difference from 0.44 to 0.30. The variance of the difference deducted was 0.20. The intra-class correlation coefficient was unknown but was assumed equal to 0.05 in the most conservative case. In each 14-day period, each investigator hospital center will recruit 15 patients, i.e. a total of 630 patients for the seven periods and the six hospital centers. These assumptions led to a statistical power estimated at 99% [39]. The required power was maximal in order to potentially perform subgroup analyses when justified.

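### The cost model's beta distributions and per-group intervals make no allowance for unit or period; if trial probabilities enter as pooled counts, precision is overstated and the groups have opposite unit mixes

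*Protocol article*

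**What the plan says.** The economic paragraph of the Statistical analysis section describes a cost-consequence analysis on a decision tree. The uncertainty method is fixed in one sentence: "All probabilities will be associated to a beta distribution and 10,000 Monte Carlo simulations will estimate the mean cost and the associated confidence interval". These results are to be given separately for the two strategies, with and without a pharmacist. A second run with other parameter values is planned "in order to consider the uncertainty due to the sample, specifically on event probabilities and individual costs induced", together with a Tornado diagram. Neither the main method nor this sensitivity analysis mentions hospital unit or period.

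The same section gives the primary outcome a logistic model with a random effect for the unit. Readmission and mortality are compared by a chi-square test and length of stay by a non-parametric test, without a unit or period term.

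The Outcomes section says avoided costs will be estimated "by using the results of a French national study concerning ADE occurrence and cost" and/or by a Delphi exercise, so part of the tree rests on outside figures.

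On the design, the article states "Every 14-day period, one further hospital unit will switch to the interventional period until all the units are in the interventional period" and plans "a total of 630 patients for the seven periods and the six hospital centers". On clustering it says: "The intra-class correlation coefficient was unknown but was assumed equal to 0.05 in the most conservative case".

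**The concern.** When a trial probability enters a decision model as a beta distribution, the usual parameters are the numbers of patients with and without the event. The spread of the draws is then that of independent patients. Here each group consists of patients from the same six units, in very unequal numbers. Early-switching units dominate the group with a pharmacist and late-switching units the group without. The group with a pharmacist also comes later in calendar time.

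If pooled counts are used, two things follow for every probability taken from the trial. The simulated distribution is too narrow, and 10,000 runs reproduce that spread without correcting it. The contrast between strategies also carries differences between units, and any time trend, that have nothing to do with the pharmacist. A second run on the same pooled basis could agree with the first and still have both problems, although the plan would read that agreement as robustness. Cost is one of the two impacts named in the Discussion, and a professional society is expected to write recommendations.

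**Working it through.** **The plan's own figure.** No precision is stated for the cost analysis. The only figure to reproduce is the 99% power in the Sample size calculation. The check used the standard stepped-wedge variance with a random unit intercept and fixed periods: 6 units, 7 periods, 15 patients per cell, variance 0.20, intra-class correlation (ICC) 0.05, difference 0.30, and two-sided 5% (assumed; not stated). The standard error (SE) is 0.0584. Power is Φ(0.30/0.0584 − 1.96) = 99.9%, which agrees with the plan, so the design inputs are read correctly.

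**Patients per unit.** With Table 1 and 15 patients per unit and period, in switch order (diabetes, cardiology, geriatric internal medicine, geriatric acute medicine, internal medicine, emergency):

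- without pharmacist: 15, 30, 45, 60, 75, 90 (total 315)
- with pharmacist: 90, 75, 60, 45, 30, 15 (total 315)

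Diabetes and cardiology make up 45/315 = 14% of the first group and 165/315 = 52% of the second. By period, the first group has 90, 75, 60, 45, 30, 15, 0 patients and the second the reverse.

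**Per-group precision under pooled counts.** Σn²/Σn = 20,475/315 = 65. The design effect is 1 + (65 − 1) × ICC, and the SE ratio is its square root. At ICC 0.05 this is 4.2 and 2.05.

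**Precision of the crude difference.** The groups share units, so the covariance is subtracted. Σ(n without × n with)/315 = 12,600/315 = 40. The variance ratio is 1 + (64 − 40) × ICC = 1 + 24 × ICC, and r is its square root. Coverage of a nominal 95% interval that ignores clustering is 2Φ(1.96/r) − 1.

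| ICC | Design effect, group | Effective n | SE ratio, group | SE ratio, difference | Coverage, difference |
|---|---|---|---|---|---|
| 0.01 | 1.64 | 192 | 1.28 | 1.11 | 92% |
| 0.05 | 4.2 | 75 | 2.05 | 1.48 | 81% |
| 0.10 | 7.4 | 43 | 2.72 | 1.84 | 71% |

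A beta-binomial simulation (100,000 runs, event probability 0.20 assumed) gave the same coverage: 92%, 81% and 71%.

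**At the plan's own rates.** Take 46% without and 46 − 30 = 16% with pharmacist.

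- The naive SE of the difference is √[(0.46 × 0.54 + 0.16 × 0.84)/315] = 0.035.
- The between-unit SD is √(0.05 × 0.20) = 0.10.
- The differences in unit weights are ±0.238, ±0.143 and ±0.048, with root sum of squares 0.398. Unit mix alone therefore adds an SD of 0.398 × 0.10 = 4.0 percentage points.
- The actual SE, with 0.10² taken out of each within-unit variance, is √[(0.2384 + 0.1244)/315 + 0.040²] = 0.052.

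**Illustration with no intervention effect.** Suppose event rates rise evenly from 10% in the first unit to 30% in the last (assumed). The pooled rates are then 73.5/315 = 23.3% without and 16.7% with pharmacist, a spurious 6.7 points. The sign reverses if the gradient reverses, and the difference vanishes if rates are unrelated to switch order.

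**The case against.** A reader might infer that a beta distribution in itself treats patients as independent. It does not. A beta can be given any mean and variance, including those of a cluster-adjusted model or an effective sample size. The article does not state the parameters, and a condensed article may leave them to the full protocol. It also lists no tree nodes, so how many probabilities come from trial patients is unknown; for outside inputs neither problem arises. This part of the objection stands, and it makes the point conditional on pooled counts. That condition is still the natural reading: pooled counts are the usual form, the intervals are per group, and the other secondary outcomes are tested without a unit term.

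A reader might also infer that the unequal unit mix biases the contrast systematically. Because the switch order is randomised, unit differences add chance error and not a bias in a known direction. Calendar time is different: the group with a pharmacist is later by design, so a time trend would not average out.

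Setting the beta from an effective sample size is only a partial answer. It leaves each group's mean tied to its own unit mix. If the groups are drawn separately, it also loses the covariance from shared units: the SE of the difference would be 2.05 times naive at ICC 0.05, where 1.48 is correct for the crude difference.

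Three limits on size are fair. The article plans intervals per group, not for a difference. The ICC of 0.05 is what the article calls its most conservative case, for the primary outcome only. The per-group figures treat the six volunteering units as a sample of units.

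**Conclusion.** The point holds conditionally. The article fixes a beta distribution for every probability and a cost interval per group, with no allowance for unit or period. If trial-derived probabilities are set from pooled counts, each group's error probability has an SE about 2.05 times the one used (1.3 to 2.7 for ICC 0.01 to 0.10). A naive 95% interval for the difference in that probability covers about 81% (92% to 71%). The groups being compared also have opposite unit mixes and different calendar times.

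This rests on pooled-count parameters, on carrying the primary outcome's ICC over to the tree's probabilities, and on the planned 315/315 split (622 patients were enrolled when the article was written). A reader might take the coverage figures as those of the cost intervals, or conclude that the economic result will be wrong. The documents do not support that: the figures concern the error probability, and unit costs and outside inputs may dominate the cost result. Since this is one secondary outcome and the repair is cheap, it is an improvement that should be made, not a flaw in the main result.

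**What to change.** State which tree probabilities come from the trial and which from outside sources, and keep beta distributions for the latter. For the trial-derived ones, replace the separate group draws as follows:

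- Fit a mixed model with intervention, unit and period terms, and draw its parameters jointly. The primary model printed in the article has no period term, so this goes one step beyond it.
- From each draw, predict the probability with and without pharmacist for the same six-unit and period mix.
- Use that one draw for both strategies in each of the 10,000 runs, so that the cost difference keeps the correct covariance.

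The cost is a little more analysis code and about two sentences of text; no new data are needed. Reported intervals will be somewhat wider. As a guide, at variance 0.20 and ICC 0.05 the SE of the difference in error probability is 0.039 with a unit term alone and 0.058 with unit and period terms, against a pooled-count value of √(2 × 0.20/315) = 0.036.
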